### 2.9. Statistical Analysis

Data will be analyzed using the Statistical Package for the Social Sciences (SPSS) for Windows (version 26; IBM, Armonk, NY, USA). Categorical data will be expressed as frequency (percentage). Continuous variables will be presented as mean ± standard deviation (SD). The normality of the data will be tested using the Shapiro–Wilk test. Effect sizes will be reported using partial eta-squared (η^2^) and interpreted according to standard conventions.

To evaluate the effects of the intervention over time, a Mixed ANOVA with a Group (intervention vs. control) × Time (baseline, post-intervention, 6 months) interaction will be conducted for all primary outcomes. Post hoc comparisons with Bonferroni correction will be performed if significant interactions are found. Secondary analyses will include intention-to-treat and per-protocol approaches as described above. Statistical significance will be established at *p* < 0.05.

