## Abstract

**Background/Objectives:** Permanent colostomy requires significant physical and psychological adaptation. Patients often experience reduced physical activity, impaired quality of life, and fear of movement. Current exercise recommendations are inconsistent, and no consensus exists on safe return to activity. This study aims to evaluate the effect of a 12-week home-based graded exercise programme on physical activity, quality of life, kinesiophobia, exercise capacity, and self-efficacy in patients with permanent colostomies. **Methods:** This randomized controlled trial will recruit 51 adults with permanent colostomies, beginning six weeks post-surgery. Participants will be randomized (1:1) to an intervention or control group. The intervention group will receive a 12-week home-based exercise programme including patient education, resistance and core training, and progressive aerobic walking. The control group will receive standard medical care and an informational leaflet. Primary outcomes include physical activity (steps/day), quality of life (Stoma-QoL), kinesiophobia (Tampa Scale), exercise capacity (6-Minute Walk Test), and self-efficacy (General Self-Efficacy Questionnaire). Follow-up will be conducted at baseline, post-intervention, and six months. Data will be analyzed using intention-to-treat principles with a significance threshold of *p* < 0.05. **Conclusions:** This trial will be the first to assess the effects of a structured, home-based graded exercise programme in individuals with permanent colostomies. The findings are expected to provide evidence on the efficacy of exercise for improving physical and psychological outcomes in this population and to inform clinical guidelines for safe, individualized activity resumption.

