#### 2.7.1. Primary Outcomes

Physical activity levels will be assessed via daily steps and energy expenditure, measured using a uniaxial accelerometer-based pedometer [39]. Participants will receive verbal and written instructions on its use. The device will be positioned at the left anterior superior iliac spine using a belt. Participants will be instructed to wear the pedometer throughout the day, except during sleep or bathing. For analysis, the mean values from the last seven consecutive days will be used. This device has demonstrated adequate reliability and validity in clinical and older populations [40,41]. The uniaxial accelerometer selected for this research has demonstrated adequate validity and reliability for step counting and energy expenditure estimation in clinical and older populations. Its simplicity and ease of use are advantageous for promoting adherence and minimizing technical difficulties in a home-based setting.

Quality of life will be assessed using the Stoma Quality of Life Questionnaire (Stoma-QoL). This disease-specific instrument has demonstrated strong reliability and validity, with good internal consistency and construct validity, and was developed to assess the physical, psychological, and social impact of living with a temporary or permanent stoma [42]. The questionnaire consists of 20 items covering domains such as social and leisure limitations, body image, physical activity, emotional wellbeing and stoma care. Each item is rated on a 4-point Likert scale ranging from “never” to “always”. Scores are transformed to a 0–100 scale, with higher values indicating better perceived quality of life. The Stoma-QoL has been validated in multiple languages, including Spanish, and demonstrates adequate reliability, making it suitable for both clinical and research settings [43,44].

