### 2.8. Sample Size Calculation

An a priori sample size calculation was based on the minimum clinically important difference (MCID) of the physical activity level interference estimated to be 1100 daily steps [57]. Using G*Power version 3.1.9.2, we obtained a sample size of 44 participants, equally distributed between the treatment and control groups, based on a confidence level of 95% (α = 0.05) and a power of 80% (β = 0.2). Anticipating a 15% dropout rate, the total sample size was increased to ensure adequate statistical power, resulting in a sample size of 51 participants.

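### Five unranked primary outcomes are each tested at 0.05 with no adjustment across them and no success rule, while the sample size rests on daily steps alone

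*Protocol article*

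**What the plan says.** The Abstract lists the five: "Primary outcomes include physical activity (steps/day), quality of life (Stoma-QoL), kinesiophobia (Tampa Scale), exercise capacity (6-Minute Walk Test), and self-efficacy (General Self-Efficacy Questionnaire"). Section 2.7.1 repeats them under its Primary Outcomes heading and gives physical activity a second measure: "Physical activity levels will be assessed via daily steps and energy expenditure". No outcome is placed above another for testing.

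Section 2.9 plans one mixed ANOVA per outcome, with the Group × Time "interaction will be conducted for all primary outcomes". It then states: "Statistical significance will be established at *p* < 0.05". The one multiplicity step is: "Post hoc comparisons with Bonferroni correction will be performed if significant interactions are found".

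Section 2.8 bases the sample size on "the minimum clinically important difference (MCID) of the physical activity level interference estimated to be 1100 daily steps", with α = 0.05 and 80% power, giving 44 evaluable participants in two equal groups, raised to 51 for 15% dropout. No other outcome enters the calculation.

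**The concern.** Five tests, each at 0.05, give five chances of a false positive under the label primary. The Bonferroni step cannot limit this: it begins only after an outcome's interaction has passed 0.05, and it works inside that outcome.

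What the five results together must show is left open. The hypothesis in the Introduction names all five without saying whether one, some or all must succeed. The Discussion treats single outcomes as enough for a conclusion: an effect on kinesiophobia alone would support bringing cognitive-behavioural principles into physiotherapy, and a confirmed effect on self-efficacy alone would support rethinking rehabilitation after colostomy.

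The stake is that the deciding outcome could be chosen after the data are seen, in a trial whose Abstract says it should inform clinical guidelines. The power statement covers only one of the five.

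**Working it through.** **Inputs.** Number of primaries: k = 5 (Abstract; Section 2.7.1). Level of each test: 0.05 (Section 2.9). Sizing: 1100 steps/day, α = 0.05, power 80%, 22 per arm (Section 2.8). The document gives no correlation between outcomes, no SD and no sidedness; values used for these are assumptions.

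**1. The plan's own figure.** The 44 can be neither reproduced nor refuted without an SD. Solving backwards with a two-sample t test, 22 per arm and 80% power:
- two-sided: d ≈ 0.865, so SD ≈ 1100/0.865 ≈ 1272 steps;
- one-sided: d ≈ 0.762, so SD ≈ 1100/0.762 ≈ 1443 steps.

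For dropout, 44 × 1.15 = 50.6, which gives 51; 44/0.85 = 51.8, which gives 52. The difference is immaterial here.

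**2. If any one significant primary supports a claim.** With all nulls true and independent tests:

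1 − (1 − 0.05)^5 = 1 − 0.774 = 22.6%.

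For correlated tests, draw Z_j = √ρ·U + √(1−ρ)·e_j for j = 1 to 5, with U and e_j standard normal, and count draws in which any |Z_j| exceeds 1.96 (one million draws per row). Because an interaction over three time points has 2 degrees of freedom, the check was repeated with 2-df chi-square statistics.

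| Assumed common correlation | At least one false positive, 1-df | 2-df |
|---|---|---|
| 0 | 22.6% | 22.6% |
| 0.3 | 20.9% | 21.1% |
| 0.5 | 18.3% | 18.6% |
| 0.7 | 14.9% | 15.2% |
| 0.8 | 12.7% | 13.0% |
| 0.9 | 10.2% | 10.4% |

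**3. If all five must be significant.** The chance of a false overall success is at most 5%. Joint power cannot exceed the power of the weakest test, so it is at most the 80% planned for steps. As an illustration, five independent tests with 80% power each (both assumptions) give 0.8^5 = 33%.

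**4. Splitting alpha instead of naming one primary.** The level becomes 0.05/5 = 0.01 each. With d ≈ 0.865 and 22 per arm, the noncentrality is 0.865 × √(22/2) ≈ 2.87 on 42 df. The two-sided critical value rises from 2.018 to 2.698, and power for steps falls from 80% to about 57%. Restoring 80% takes 33 per arm: 66 evaluable, and 66/0.85 = 77.6, so 78 recruited. If the sizing was one-sided (d ≈ 0.762), the corresponding fall is from 80% to about 55%.

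**The case against.** The strongest objection is that the protocol states no any-one rule. The hypothesis, the opening of the Discussion and the Conclusions all join the five outcomes with an and. Read as a joint requirement, that wording carries no inflation of false-positive error. This stands in part: no inflated rate can be stated as the trial's error rate without a condition. It does not remove the problem, because the Discussion also draws conclusions from single outcomes, and a joint requirement is not what the sample size was built for.

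A reader might also count energy expenditure as a sixth primary and infer an error rate of up to 1 − 0.95^6 = 26.5%. The document does not support that figure. The Abstract defines the physical activity outcome as steps/day only. Both measures come from one pedometer, so independence is implausible: with those two correlated at 0.9 and all else independent, six tests give about 24%. The discrepancy between the Abstract and Section 2.7.1 needs reconciling, but it does not set the size of the problem.

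A reader might likewise say there is no multiplicity control at all. That is too broad: Bonferroni is planned, but not across outcomes.

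Finally, detailed multiplicity procedures are often left to an analysis plan, which is not shown. That is fair for the choice of procedure. But the unranked list of primaries, the 0.05 threshold and the sizing on a single outcome are all fixed in this document.

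**Conclusion.** The point holds in conditional form. Five unranked primaries are tested at 0.05 each with no adjustment across them, no success rule, and sizing on one of them. If one significant outcome may carry a claim, the chance of at least one false-positive primary under the global null is about 10% to 23%, at least twice the nominal 5% throughout the range. It rests on assumed common correlations of 0.9 to 0. If all five are required, type I error is controlled, but the 80% power applies to steps only and not to the joint claim. Either reading calls for a change.

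The 57% power figure for an alpha split is illustrative, since it depends on a standardised effect solved backwards from 22 per arm with a two-sided t test.

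**What to change.** In the Abstract, Section 2.7.1 and Section 2.9, name mean steps/day at the end of the 12-week programme as the single primary outcome, tested two-sided at 0.05. It is the outcome already used for sizing. Make Stoma-QoL, TSK-11, 6MWT, self-efficacy and energy expenditure secondary, either with Holm adjustment across them or reported as estimates with 95% confidence intervals and no confirmatory claim. Temper the single-outcome conclusions in the Discussion to match.

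State in Section 2.8 that the calculation is two-sided. If it was in fact one-sided, a two-sided test with 22 per arm would have about 69% power at the implied d ≈ 0.762, and the sample size would need another look.

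As a matter of headings only, adherence, satisfaction and feasibility could also move out of the Primary Outcomes section; Section 2.7.1 already treats feasibility as descriptive.

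The cost is wording: alpha and N = 51 stay as stated, no extra data are needed, and the Data Availability statement says none have been collected. The downside is the loss of any unadjusted confirmatory claim on the other four domains. An all-must-succeed rule, a fixed testing order or Holm across the five would also answer the point. The first and last would need the power reconsidered; a fixed order starting with steps would keep the power for steps only.

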The selection of study variables was based on the multifactorial nature of adaptation following colostomy. Physical activity was included as a primary indicator of behavioural change and global recovery, since reduced activity levels have been consistently linked to postoperative complications and poorer health outcomes [26,27,28]. Quality of life represents a central construct integrating physical, psychological, and social dimensions, which are often impaired in this population. Kinesiophobia, or fear of movement, was incorporated because it constitutes a psychological barrier to physical rehabilitation and has been associated with decreased participation and delayed functional recovery in various clinical populations [29,30]. Exercise capacity, measured through the Six-Minute Walk Test, provides an objective index of functional performance and tolerance to physical effort [31]. Finally, self-efficacy was selected as it reflects patients’ confidence in managing their condition and performing physical activity safely, a critical determinant of adherence and long-term lifestyle modification [32]. Together, these outcomes provide a comprehensive assessment of both physical and psychological domains relevant to recovery after permanent colostomy.

Given the heterogeneity of exercise recommendations for permanent colostomy patients, personalized home-based programmes are required to reduce barriers and improve adherence. The present study aims to evaluate the effect of a home-based gradual exercise programme on physical activity, quality of life, kinesiophobia, exercise capacity, and self-efficacy in individuals with permanent colostomies. A six-month follow-up will also be conducted to assess patient adherence and programme satisfaction. We hypothesize that participants who complete the 12-week home-based gradual exercise programme will demonstrate greater improvements in physical activity levels, quality of life, kinesiophobia, exercise capacity, and self-efficacy compared with those receiving standard medical care.

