## 3. Results

The results will be published as a peer-reviewed article. The authors intend to include three tables summarizing the main results of the study. The first will present the descriptive characteristics of the sample. The second will report the baseline group comparisons for the primary outcomes. The third table will display the post-intervention results, including both within-group and between-group changes, and the effect sizes will be calculated using Cohen’s d. Additionally, a figure depicting the study flow diagram will be provided.

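### The test for every primary outcome is a 2-df Group × Time interaction that must be significant before any time point is compared; a baseline-adjusted post-intervention difference would answer the trial's question more directly and often with more power.

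*Protocol article*

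**What the plan says.** Section 2.9 states that "a Mixed ANOVA with a Group (intervention vs. control) × Time (baseline, post-intervention, 6 months) interaction will be conducted for all primary outcomes". With two groups and three visits, that interaction has (2−1)(3−1) = 2 degrees of freedom, and baseline is one of the three outcome levels. No baseline covariate is named. The same section continues: "Post hoc comparisons with Bonferroni correction will be performed if significant interactions are found". The number of comparisons is not given. Its effect measure is partial eta-squared.

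Three other places bear on which contrast matters:

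- The hypothesis in the Introduction is about greater improvement than standard care among those who complete the 12-week programme.
- Section 2.8 sizes the trial on a "minimum clinically important difference (MCID) of the physical activity level interference estimated to be 1100 daily steps", with 44 participants split equally, α = 0.05 and 80% power.
- Section 3 says that "The third table will display the post-intervention results, including both within-group and between-group changes, and the effect sizes will be calculated using Cohen’s d".

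No section names a primary time point.

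**The concern.** The plan's question and its test do not line up. The hypothesis, the sizing and the results table all lead to one quantity, the difference between groups after the programme. The decision rule is a non-directional test spread over three visits, and the contrast of interest is tested only as a follow-up step with a corrected threshold.

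Two things are at stake. The first is power. Two numerator degrees of freedom, and an effect that may partly fade once support ends, can leave the interaction non-significant although the groups differ at 12 weeks. The second is interpretation. The F test and partial eta-squared are not in steps/day, so the result that carries the inference cannot itself be read against 1,100 steps. Baseline steps, which would sharpen the 12-week comparison as a covariate, are already collected.

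**Working it through.** **Plan's own figure.** The 44 participants cannot be reproduced forward, because section 2.8 gives no SD, no sidedness and no test. Back-solving a two-sided two-sample t test at α = 0.05, 22 per arm and 80% power gives d = 0.865, that is SD = 1100/0.865 ≈ 1272 steps. A one-sided test would give d = 0.762 and SD ≈ 1443. I use d = 0.865 below as an assumption.

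**Further assumptions.** 22 evaluable per arm; equal variances and equal correlation ρ between visits (compound symmetry). The plan gives no ρ, so I vary it.

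**Interaction test.** F with 2 and 2 × (44−2) = 84 df. With δ the group difference at each visit in SD units, the noncentrality is λ = (22/2) × Σ(δ − mean δ)² / (1−ρ).

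- Effect fully kept, δ = (0, d, d): Σ = (2/3)d² = 0.498. At ρ = 0.5, λ = 11 × 0.498/0.5 = 10.97, power 0.838.
- Effect fully lost, δ = (0, d, 0): the same Σ, hence the same power.
- Half kept, δ = (0, d, d/2): Σ = 0.5d² = 0.374, λ = 8.22, power 0.714.
- Growing to 1.5 times, δ = (0, d, 1.5d): Σ = 1.167d² = 0.872, λ = 19.19, power 0.978.

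**Baseline-adjusted 12-week comparison (ANCOVA).** F with 1 and 41 df, λ = (22/2) × d²/(1−ρ²). At ρ = 0.5, λ = 11 × 0.748/0.75 = 10.97, power 0.898. This does not depend on what happens at 6 months. At ρ = 0.5 with a sustained effect the two tests have the same λ, so the gap of 6 points is the price of the second degree of freedom.

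| ρ | Interaction: kept or lost | half kept | grows | ANCOVA at 12 weeks |
|---|---|---|---|---|
| 0.3 | 0.691 | 0.558 | 0.913 | 0.835 |
| 0.5 | 0.838 | 0.714 | 0.978 | 0.898 |
| 0.7 | 0.972 | 0.913 | 0.999 | 0.975 |
| 0.8 | 0.998 | 0.985 | 1.000 | 0.997 |

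**Full route to a 12-week conclusion.** This requires a significant interaction and then a significant 12-week contrast. Three comparisons are assumed, so the threshold is 0.05/3 = 0.0167. Power comes from 20,000 simulated trials per scenario, with a sustained effect:

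| ρ | contrast on change from baseline | unadjusted 12-week contrast | ANCOVA (simulated) |
|---|---|---|---|
| 0.5 | 0.646 | 0.563 | 0.891 |
| 0.7 | 0.882 | 0.627 | 0.972 |
| 0.8 | 0.976 | 0.646 | 0.996 |

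Without the Bonferroni step the ρ = 0.5 figures are 0.758 and 0.687. If correlation decays with time (first-order autoregressive, ρ = 0.5), the corrected figures are 0.622 and 0.518.

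**The case against.** The case for the plan as written is substantial.

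- **Validity.** A Group × Time interaction in a randomised trial is a legitimate test that uses change from baseline. No bias or type I error inflation is shown. Section 2.9 aims at effects over time, and no section fixes 12 weeks as primary. This stands: the point is efficiency and fit to the question.
- **Benchmark.** The 0.865 SD is not the sponsor's figure. If the software's within-between interaction option was used, 44 participants correspond to f = 0.194 (three visits, correlation 0.5), and the interaction would have 80% power by design. This stands, so the power figures are conditional.
- **Generality.** The interaction loses almost nothing at correlation 0.7 or more with a sustained effect, and gains if the effect grows. This stands too.

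A reader might also infer more than the documents support:

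- That the plan yields no estimate to compare with 1,100 steps, or forbids looking at 12 weeks after a non-significant interaction. Section 3 plans between-group post-intervention changes without that condition. What is missing is a baseline-adjusted difference with CI, named as the main inference and free of the interaction test.
- That a significant interaction leaves timing and direction unknown. The post hoc comparisons exist to answer that.
- That the 6-month visit is contradictory. The Introduction says "A six-month follow-up will also be conducted to assess patient adherence and programme satisfaction", but the word also does not exclude other measures, and the Abstract lists six months among the assessments.
- That partial eta-squared and Cohen's d conflict. One can describe the ANOVA and the other the pairwise changes.

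**Conclusion.** The point holds as one of efficiency and of matching the test to the question. Section 2.9 fixes a 2-df test with baseline as an outcome level and makes the time-point comparisons conditional and then corrected, while the rest of the article points to a post-intervention difference. It does not hold as a claim that the analysis is invalid or that it always costs power.

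At d = 0.865 and correlation 0.5, the loss on the interaction alone is about 6 points if the effect is fully kept or fully lost at 6 months (84% against 90%) and about 18 points if half is kept (71% against 90%). The whole route to a 12-week conclusion has about 56–65% power with a sustained effect, below the planned 80%. The loss on the interaction alone vanishes at correlation 0.7 with a sustained effect and reverses if the effect grows by 6 months. On the whole route it falls to about 2 points at correlation 0.8, provided that the contrast is on change from baseline. All these figures rest on the back-solved effect size, the assumed correlation structure and, for the whole route, three comparisons.

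**What to change.** In section 2.9, for each of the five primary outcomes, name the baseline-adjusted between-group difference at post-intervention, with 95% CI, as the main estimate. Obtain it from ANCOVA, or from a mixed model on the two post-baseline visits with group, visit, group × visit and the baseline value as covariate. Read the steps/day estimate against 1,100 steps, since that is the outcome on which the trial is sized; the other four keep their stated status. Report the 6-month contrast as secondary, and make neither contrast conditional on the interaction p-value. For clarity, state in the Introduction that the 6-month visit also measures these outcomes, and say which effect size belongs to which analysis.

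The cost is wording and one degree of freedom; baseline is already collected, and the article says that no data exist yet. The downside is less power than the interaction test if the effect mainly appears or grows at 6 months.

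### The Abstract makes intention-to-treat the analysis principle, but section 2.9 ranks it as secondary to a three-visit mixed ANOVA that names no population and, unless values are imputed, omits anyone with a missed visit

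*Protocol article*

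**What the plan says.** The Abstract states one principle and names no other population: "Data will be analyzed using intention-to-treat principles with a significance threshold of" p < 0.05.

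Section 2.9 (Statistical Analysis) specifies the main test: "a Mixed ANOVA with a Group (intervention vs. control) × Time (baseline, post-intervention, 6 months) interaction will be conducted for all primary outcomes". It does not say which patients enter that test. Shortly afterwards it adds: "Secondary analyses will include intention-to-treat and per-protocol approaches as described above".

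The hypothesis at the end of the Introduction is that "participants who complete the 12-week home-based gradual exercise programme will demonstrate greater improvements" than those receiving standard care.

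The Abstract lists the assessments: "Follow-up will be conducted at baseline, post-intervention, and six months". Section 2.8 expects losses: "Anticipating a 15% dropout rate, the total sample size was increased to ensure adequate statistical power, resulting in a sample size of 51 participants".

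**The concern.** If ITT is a secondary analysis, the main ANOVA is by implication something else, and the article does not say what. The sentence that should settle this refers back to text that does not exist. An analysis plan written from this article could follow either ranking. If nothing else fixes the choice, it could be made after the results are seen.

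The named method makes this matter in practice. A mixed ANOVA in its classical form uses only patients with a value at every time point. A patient measured at the end of the 12-week programme who then misses the 6-month visit would lose the 12-week measurement too. Section 3 plans a results table on post-intervention changes, so the loss would reach a headline comparison. If missing visits are related to how patients are doing, and differ between arms, the comparison of those who remain is no longer protected by randomisation.

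**Working it through.** **1. Who is analysed, place by place**

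| Place | Statement |
|---|---|
| Abstract | ITT, for the data in general |
| 1. Introduction, hypothesis | Programme completers against standard care |
| Sections 2.1 to 2.8 | Neither ITT nor per-protocol is mentioned |
| 2.9, main test | Mixed ANOVA for all primary outcomes; no population named |
| 2.9, later sentence | ITT and per-protocol both secondary, by reference to earlier text |

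The Abstract phrase is the only earlier mention of ITT, and it defines neither a population nor a missing-data rule. Per-protocol appears only in 2.9. The back-reference therefore has no target, and the two ranks of ITT cannot both stand.

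**2. What the named test needs**

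The factor Time has three levels. The classical repeated-measures procedure in SPSS (GLM) removes a case with any missing level unless values are filled in first. Section 2.9 mentions no imputation. The deletion acts on missed assessments, in both arms. It does not act on stopping the exercises: a patient who stops but attends all three visits stays in the analysis, in the assigned arm.

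**3. How many patients**

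Inputs from section 2.8: 44 required, 15% dropout, 51 to be randomised.

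- The plan's own figure: 44 × 1.15 = 50.6, rounded up to 51. Dividing instead, 44 / 0.85 = 51.8, gives 52. The stated 51 is reproduced by the first route and is one patient below the second.
- Complete cases at 15% dropout: 51 × 0.85 = 43.35, about 43 analysed and about 8 omitted.
- Against the requirement: 43 compared with 44.

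Power, as a check. No SD is given, so the effect size has to be back-solved. With 22 per arm, a two-sided t-test at α = 0.05 and 80% power, the standardised difference is 0.865, which implies an SD of 1,100 / 0.865, about 1,272 steps. At that effect size power is about 86% with all 51 patients, 80% with 44, and about 79% with 43.35. The planned loss therefore costs almost nothing against the 80% target.

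**4. Can bias arise, and in which direction?**

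Illustration under assumptions that are not in the protocol: no true effect; unit SD at each visit; correlation 0.6 between visits; 26 and 25 patients per arm; the 8 intervention patients with the poorest change at 12 weeks miss the 6-month visit.

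- SD of change = √(1 + 1 − 2 × 0.6) = √0.8 = 0.894.
- Removing the lowest 8 of 26 (fraction 0.308, cut-point z ≈ −0.50) shifts the mean change of the remaining patients by about 0.894 × 0.352 / 0.692 ≈ 0.45 SD, where 0.352 is the normal density at the cut-point.
- Simulation with 4,000 replicates: 0.44 SD using complete cases only (43 patients), 0.00 SD using every observed 12-week value.

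This pattern is deliberately extreme, so it shows the mechanism and not an expected size. By symmetry, if the 8 best-changing intervention patients were the ones missing, the shift would have the opposite sign.

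**The case against.** The strongest reply is that listwise deletion is nowhere stated. The article names a test but not its missing-data handling, and a condensed article may leave imputation to an analysis plan that is not shown. That stands: exclusion of patients with a missed visit is a conditional risk, and silence on imputation is not in itself a fault. One could also read the 2.9 sentence as meaning that the same ANOVA will be run on two populations. Neither reply removes the conflict with the Abstract or supplies the missing description, and neither says which population is primary.

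Three stronger readings are tempting, and the documents do not support them.

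- A reader might infer from the hypothesis that the main test compares programme completers with all controls. That wording sits in the Introduction and defines no analysis set, and the ANOVA needs complete visits, not a completed programme.
- A reader might infer that the result will favour the exercise arm. Section 4 says that impairments may limit participation and that motivation depends on perceived benefits and barriers, so outcome-related dropout is plausible. But no section gives reasons for missed visits by arm. Loss of controls, or of patients who recover well, could act the other way.
- A reader might put a size on the bias by assuming that exercise-arm dropouts gain nothing and are never measured again, or might compound the 15% over two follow-up visits. The first pattern is not repaired by a mixed model, because patients with only a baseline value add essentially no information on the treatment effect. The second needs a further loss that the article does not give; its single 15% may already cover the whole study.

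**Conclusion.** The concern holds in conditional form. That ITT has two ranks and that the back-reference is empty are matters of text and need no assumption. Given a classical ANOVA without imputation, about 43 of 51 patients would be analysed at the protocol's own dropout rate, and any observed 12-week values of those omitted would be lost. What is at stake is possible bias of unknown direction and wasted data. Power is not the issue, because section 2.8 already provides for this loss. The size of any bias cannot be derived from the article.

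**What to change.** In section 2.9:

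- Make ITT the primary analysis: all randomised patients, analysed in the arm assigned.
- Replace the mixed ANOVA with a linear mixed model for repeated measures on every observed value, with group, visit and group × visit, and with adjustment for baseline. SPSS MIXED fits this, so the software need not change. Alternatively, keep the ANOVA and state the imputation rule.
- Define per-protocol and make it supportive only.
- Complete the back-reference or delete it.

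In the Introduction, word the hypothesis in terms of participants allocated to the programme, not those who complete it.

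Possible wording for 2.9:

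> The primary analysis will follow intention-to-treat: every randomised patient is analysed in the assigned arm. A linear mixed model with group, visit and their interaction, adjusted for baseline, will use all observed post-intervention and 6-month values. A per-protocol analysis, with its population defined in advance, will be supportive.

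The Data Availability statement says that no data have yet been collected, so the change costs only wording and slightly more analysis work. The price is reliance on the missing-at-random assumption: the model keeps 12-week data that the ANOVA would discard, but it cannot recover outcomes of patients who are never measured after baseline.
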